### Interim analyses {21b}

Not applicable.

### Methods for additional analyses (e.g., subgroup analyses) {20b}

No additional analysis will be performed.

### Analysis methods to address protocol non-adherence and statistical methods to handle missing data {20c}

In cases of dropout or withdrawal from the study, the data will be assessed by intention-to-treat analysis. Participants that leave the study without performing the 18 proposed sessions (due to sickness, moving to another town, inability to attend sessions) will be considered protocol deviations.

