**Methods:**

This is a randomized, controlled, double-blind, and parallel clinical trial that will include 56 participants, over 40 years old, with radiographic evidence of thumb base osteoarthritis. Participants will be randomly allocated into two groups: control and intervention. The following evaluations will be conducted: the Australian/Canadian Hand Osteoarthritis Index, Canadian Occupational Performance Measure, Nine-Hole Peg Test, grip and pinch strength associated with muscle activation assessment, and Bilateral Upper Limb Function Test at four different times: baseline, session 13, session 18, and follow-up. Treatment will take place over 6 weeks, with reassessments in the fourth and sixth weeks and 3 months after the end of the intervention (follow-up). Qualitative variables will be expressed as frequency and percentage, and quantitative variables as mean and standard deviation. Intergroup comparison of the intervention will be performed by repeated measures ANOVA, considering the effect of the two groups and four assessments, and interactions between them.

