### Sample size {14}

A priori sample calculation was performed in the Gpower 3.1.5 software, considering the comparison of two independent groups (control and intervention) in four distinct stages (pretreatment, 13th and 18th assessment, and follow-up). The statistical test that will be applied was also taken into account, that is, repeated measures analysis of variance (ANOVA) for the variables of interest (pain, manual dexterity, function, strength, and muscle activation). It was considered an effect size of 0.25, 5% significance, and power of 90%, resulting in 46 participants (23 per group). Considering possible sample losses, we will evaluate 20% more, that is, 56 subjects divided into two groups of 28 each.

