## Statistical methods

### Statistical methods for primary and secondary outcomes {20a}

Data will be analyzed according to the intention-to-treat principle. All trial outcomes will be blinded for treatment allocation, and all participants will be analyzed in the treatment group to which they were originally randomized. Statistical analysis will be performed using the Statistical Package for the Social Sciences, version 19.0 (SPSS Inc., Chicago, IL, USA). A 5% significance level will be adopted for all analyses. The normality of the residues will be verified by the Shapiro-Wilk test. Pain, function, activity and participation, grip and pinch strength, dexterity, and muscle activation will be compared between the groups (control and intervention) and stages (pretreatment, 4- and 6-week assessments, follow-up), and interactions between them analyzed by mixed model ANOVA considering group and time factors for repeated measures if the residuals exhibit normality with post hoc contrasts (treated versus control group).

The first statistical procedure will be to verify, in general and at each assessment stage (pretreatment, 13th and 18th assessment, follow-up) if pain, function, activity and participation, grip and pinch strength, dexterity, and muscle activation differ between the intervention and control groups. The second statistical procedure aims to verify whether pain, function, activity and participation, grip and pinch strength, dexterity, and muscle activation change over the four assessment stages (pretreatment, 4- and 6-week assessments, follow-up) within each group.

The quantitative variables will be expressed as minimum and maximum values, means, medians, standard deviations, coefficients of variation, and asymmetry coefficients. Categorical variables will be expressed as frequencies and percentages.

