#### Adverse event reporting and injuries {22}

If a participant withdraws from the trial, the reasons for withdrawal will be recorded, and all information provided up to the time of their withdrawal will be kept secret, maintaining data confidentiality. Strategies to maximize follow-up and prevent missing data will be used, including adhering to the assessment schedule in the event of participant withdrawal. Participants who withdraw from the trial will not be replaced.

All the medical records of volunteers will be carefully assessed, and any injuries or complications of the treatment, if any, will be reported along with the trial results. Injuries will be categorized as serious and minor adverse events.

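### The protocol promises intention-to-treat analysis of everyone randomised, but does not settle whether its repeated measures ANOVA keeps participants who miss a visit

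*Protocol article*

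**What the plan says.** Four places in the protocol article bear on this.

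- Section {20c}, on non-adherence and missing data: "In cases of dropout or withdrawal from the study, the data will be assessed by intention-to-treat analysis". It adds only that leaving before all 18 sessions counts as a protocol deviation.
- Section {20a}: "all participants will be analyzed in the treatment group to which they were originally randomized". The method there is "mixed model ANOVA considering group and time factors for repeated measures if the residuals exhibit normality", followed by treated-versus-control contrasts. The software is SPSS 19.0, with no procedure named.
- Abstract, Methods: "Intergroup comparison of the intervention will be performed by repeated measures ANOVA, considering the effect of the two groups and four assessments".
- Sample size {14}: "The statistical test that will be applied was also taken into account, that is, repeated measures analysis of variance (ANOVA", with four stages. It then says: "Considering possible sample losses, we will evaluate 20% more, that is, 56 subjects divided into two groups of 28 each".

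All primary outcomes are changes from baseline to week 6 (Outcomes {12}). The model also spans the follow-up at week 18. The section on adverse events {22} intends to keep to the assessment schedule after a participant withdraws.

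**The concern.** Intention-to-treat fixes the arm in which a person is counted. It does not say how a record with a missing visit enters a repeated measures test. In the classical group-by-time ANOVA each participant is one row with a value at every stage, and a row with a gap is removed whole.

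On that reading, someone measured at week 6 but lost before week 18 contributes nothing to the week-6 comparison, although the primary value was collected. For pain and AUSCAN function, a missed week-4 visit has the same effect. Something that happens after the primary time point can then decide who counts at that time point. If those who are doing badly are likelier to leave, the comparison is selected on outcome and is a completers' analysis reported as intention-to-treat. Values collected after withdrawal would also go unused whenever one other visit is missing.

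**Working it through.** **1. The texts side by side.** {20a} and {20c} require every randomised participant in the analysis. The Abstract and {14} name a test that, run classically, cannot include incomplete records. The term in {20a} is used both for the mixed-design (between-within) ANOVA and for a linear mixed model, and SPSS offers procedures for both. The document does not choose.

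**2. The plan's own figure.** 46 × 1.20 = 55.2, rounded up to 56 (28 per arm). This reproduces. With 20% of 56 lost, 56 × 0.80 = 44.8, so about 45 complete records.

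**3. Participants with a week-6 value who would be deleted.** The protocol gives no loss by visit, so each pattern below is an assumption.

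| Assumed loss | Seen at week 6 | Complete | Deleted despite week-6 value |
|---|---|---|---|
| Dropout without return: 5% by week 6, 10% in total by week 18 | 56 × 0.95 = 53.2 | 56 × 0.90 = 50.4 | 2.8 |
| 10% by week 6, a further 10% by week 18 | 56 × 0.90 = 50.4 | 56 × 0.80 = 44.8 | 5.6 |
| Independent misses: 5% week 4, 5% week 6, 10% week 18 | 56 × 0.95 = 53.2 | 56 × 0.95 × 0.95 × 0.90 = 45.5 | 7.7 |
| 5% by week 6, a further 15% by week 18 | 56 × 0.95 = 53.2 | 56 × 0.80 = 44.8 | 8.4 |

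The range is about 3 to 8 people. The independent-misses row applies to pain and AUSCAN only: Table 1 and the Four-week assessment section schedule no week-4 pinch strength or muscle activation. Loss before week 18 still removes those records.

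**4. Illustrative bias in the week-6 difference.** Assumptions: week-6 pain means 40 and 30 mm, SD 19.8 mm, true difference 10 mm. The probability of loss after week 6 is logistic in the week-6 score y: p(y) = 1/(1 + exp(−a − b·y)), with b = ln(OR)/20, where OR is the odds ratio of loss per 20 mm. The mean among completers in each arm is E[y(1 − p)] / E[1 − p].

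| Loss after week 6 | OR per 20 mm | Completers' difference | Attenuation |
|---|---|---|---|
| 16% on average | 1.5 | 9.8 mm | 2% |
| 10% on average | 2.2 | 9.5 mm | 5% |
| 19% control, 12% intervention | above 3 | 8.7 mm | 13% |

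A separate simulation on a standardised scale (effect −0.60, correlation 0.5, about 13% lost, likelier with worse week-6 pain) gave −0.60 from everyone seen at week 6 and −0.57 from completers, about 5%.

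**5. Power.** Noncentral-F power for the group-by-time test at f = 0.25 and alpha 0.05, assuming correlation 0.5 because none is stated: at N = 44, 45 and 46 it is 0.900, 0.906 and 0.913 with two measurements, and 0.982, 0.984 and 0.986 with four. Falling from 46 to about 45 costs almost nothing.

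**The case against.** The strongest reply is that {20a} governs the analysis, that its wording can mean a linear mixed model, and that on that reading nobody is deleted. The Abstract is a summary and {14} describes a completed calculation, so neither clearly overrides {20a}. {20a} also plans a group comparison at each stage, which could be run on all participants seen at that stage. This stands as far as it goes: listwise deletion is a possible reading, not a stated rule. It does not remove the point, because {14} calls repeated measures ANOVA the test to be applied and nothing in {20a} or {20c} says that incomplete records are kept.

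A reader might infer from the extra 20% that the sponsor expects lost participants to leave the analysis. That does not follow, since enrolment is inflated for attrition under mixed models too.

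A reader might also say that the procedure, covariance structure and imputation rules belong in an analysis plan that is not shown. That is right, and their absence is not the point made here. The point is that the stated principle and the stated test do not fit together within this document.

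Finally, the larger bias figure needs loss that depends strongly on outcome. Milder assumptions give 2% to 5%.

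**Conclusion.** The point holds as an unresolved conflict. Sections {20a} and {20c} promise analysis of all randomised participants, the Abstract and {14} name a method that classically drops incomplete records, and the wording of {20a} does not decide between them. It would go too far to say that the protocol commits to a completers-only primary analysis.

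If the classical method is used, about 3 to 8 of 56 participants with week-6 data would be dropped under the loss patterns tried. With outcome-dependent dropout, the week-6 effect would be understated by about 2% to 13% in these illustrations. All of these sizes rest on assumed patterns. At the planned 20% loss the harm is mainly to the intention-to-treat claim and through possible bias. The power cost is small. The wording should be corrected before analysis.

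**What to change.** In the Abstract, {20a} and {20c}, state that the analysis is a likelihood-based linear mixed model for repeated measures (for example the SPSS MIXED procedure). It should use every visit obtained from every randomised participant, including visits after treatment stopped, with the week-6 group contrast as primary and no participant dropped for a missing visit. For pinch strength and muscle activation, list only the visits at which they are measured.

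Leave the calculation in {14} as the repeated measures ANOVA approximation on which the size was based, and add one sentence that the analysis will be the mixed model. Rewording it as if the calculation had used a mixed model would misdescribe how 46 was obtained.

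The cost is wording only: the same software and data, with no extra visits or participants.

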### Plans to give access to the full protocol, participant-level data, and statistical code {31c}

Not applicable.

### Oversight and monitoring

#### Composition of the coordinating center and trial steering committee {5d}

A principal investigator (blind evaluator) and two coordinators who will coordinate all phases of the study and be responsible for statistical analysis and data interpretation will develop the study.

#### Composition of the data monitoring committee, its role, and reporting structure {21a}

There will be no data monitoring committee since only the primary evaluator and two study coordinators will have access to the clinical trial data.

#### Adverse event reporting and injuries {22}

If a participant withdraws from the trial, the reasons for withdrawal will be recorded, and all information provided up to the time of their withdrawal will be kept secret, maintaining data confidentiality. Strategies to maximize follow-up and prevent missing data will be used, including adhering to the assessment schedule in the event of participant withdrawal. Participants who withdraw from the trial will not be replaced.

All the medical records of volunteers will be carefully assessed, and any injuries or complications of the treatment, if any, will be reported along with the trial results. Injuries will be categorized as serious and minor adverse events.

#### Frequency and plans for auditing trial conduct {23}

Fortnightly meetings will be held with the group of researchers involved in the study in order to discuss the development of the study or other questions/doubts. An independent researcher will verify the data collected during the study. If any documents are missing or information is inconsistent, the local ethics committee will be notified. Finally, if there is any change in the study, the ethics committee, the journal, and the Brazilian Registry of Clinical Trials (ReBEC) will be notified immediately.

#### Plans for communicating important protocol amendments to relevant parties (e.g., trial participants, ethical committees) {25}

All amendments to the protocol will be communicated and approved by the Human Research Ethics Committee from the Federal University of São Carlos (UFSCar) – SP.

#### Dissemination plans {31a}

The results of this randomized controlled clinical trial are expected to be disseminated through presentations at national conferences and congresses and publication in peer-reviewed journals.

## Discussion

This study will demonstrate whether specific strengthening of the first dorsal interosseous muscle has a superior and positive effect on the clinical picture of patients with CMC OA. Additionally, if specific strengthening of this muscle is not superior to the traditional protocol in the literature, it will also be determined whether the two protocols are equivalent in terms of the best clinical picture. This will be analyzed based on possible changes in some symptoms (i.e., pain, function, activity, and participation) during the treatment period (4 weeks and 6 weeks), or 3 months after its completion.

To date, there are no guidelines for the treatment of CMC OA. The most recent update of treatment recommendations comes from the EULAR, which published an update on management recommendations for patients with hand osteoarthritis in 2018 [11]. However, the only recommendation for patients with OA at the base of the thumb is the use of orthosis for symptom relief. In general, the article indicates that the main goal of hand osteoarthritis treatment is to control symptoms such as pain and stiffness and optimize hand function in order to maximize activity, participation, and quality of life. Following this principle and developing a protocol involving muscle strengthening through functional activities in specific cases of CMC OA seems to be important. In addition, our protocol involves strengthening a muscle considered fundamental in stabilizing the joint involved, a significant differential.

Finally, it is worth mentioning that systematic reviews on the subject emphasize the low quality of clinical trials, which can interfere with the reliability and clinical applicability of manual exercises. As such, our protocol could contribute to the development of a reliable methodological procedure to guide physiotherapists in clinical practice, providing clear information on how to perform the exercises, training volume, and load progression.

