**Discussion:**

This study will demonstrate whether the specific strengthening of the first dorsal interosseous muscle has a superior and positive effect on the clinical picture of patients with CMC OA. Additionally, if specific strengthening of the muscle is not superior to the traditional protocol in the literature, it will also be determined whether the two protocols are equivalent in terms of the best clinical picture.

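### The article promises to determine equivalence if superiority is not shown, but its stated tests and sample size address only a difference

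*Protocol article*

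**What the plan says.** The Abstract (Discussion paragraph) and the main Discussion set out the same two-step reading of the trial. The first step is superiority. The second, triggered "if specific strengthening of the muscle is not superior to the traditional protocol in the literature", is that "it will also be determined whether the two protocols are equivalent in terms of the best clinical picture". The main Discussion then indicates the basis: "This will be analyzed based on possible changes in some symptoms", naming pain, function, activity and participation, "during the treatment period (4 weeks and 6 weeks), or 3 months after its completion". No one outcome or time point is singled out.

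The operative sections contain nothing that matches the second step:

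- Objectives {7} ask whether the new programme is effective and compare the groups. Equivalence is not an objective.
- Statistical methods {20a} have the outcomes "analyzed by mixed model ANOVA considering group and time factors for repeated measures", with post hoc contrasts of treated against control. The first procedure asks whether outcomes up to and including "muscle activation differ between the intervention and control groups". Also: "A 5% significance level will be adopted for all analyses".
- Sample size {14} is computed for the repeated-measures ANOVA only: effect size 0.25, 5% significance, 90% power, 46 participants, raised to 56 (28 per arm).

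**The concern.** A test for a difference can end in two ways: a difference is shown, or it is not. The second ending does not say that the difference is small. It says only that zero cannot be ruled out, and in a trial of this size differences well away from zero may not be ruled out either. To conclude equivalence, one has to show that the confidence interval lies inside a margin fixed in advance. The stated methods contain no step of that kind.

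Both arms receive active exercise, so a result that does not separate them is a realistic possibility. The Discussion hopes that the protocol will guide physiotherapists in practice. What the trial may conclude from a null result therefore matters to its readers.

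**Working it through.** **1. The plan's own figure.** Inputs from Sample size {14}: effect size 0.25 (read as the ANOVA effect size f), 5% significance, 90% power, 2 groups, 4 measurements. The correlation between measurements and the ANOVA term tested are not stated. Using noncentral F power:

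- Group effect, correlation 0: N = 46, power 91.3%.
- Interaction, correlation 0.2 to 0.25: N = 48 to 44.
- At correlation 0.5: N = 30 for the interaction and 108 for the group effect.

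So 46 is attainable but cannot be verified from the article. 46 × 1.2 = 55.2, which gives 56. Under every reading this is a sample size for detecting a difference.

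**2. Precision of a between-group comparison at one time point, in SD units.** SE = √(2v/n), with v = 1 unadjusted and v = 1 − ρ² after adjustment for baseline (0.75 at ρ = 0.5; 0.51 at ρ = 0.7). The values of ρ are assumptions. The 90% interval that corresponds to two one-sided 5% tests has half-width t(0.95; 2n − 2) × SE.

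- 23 per arm, unadjusted: 1.680 × √(2/23) = 0.50 SD.
- 28 per arm, unadjusted: 1.674 × √(2/28) = 1.674 × 0.267 = 0.45 SD.
- 28 per arm, ρ = 0.5: 1.674 × √(1.5/28) = 0.39 SD.

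Equivalence is shown only if |observed difference| + half-width is less than the margin. Unadjusted, the half-width alone uses up almost all of a 0.5 SD margin.

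**3. Power to show equivalence if the arms are truly identical.** This is the probability that |d| + t(0.95; 2n − 2) × (estimated SE) < margin, with d normal around 0 and the variance estimate on 2n − 2 degrees of freedom. The margins are assumed, because the article states none. For 28 per arm:

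| Margin (SD) | Unadjusted | Adjusted, ρ = 0.5 | Adjusted, ρ = 0.7 |
|---|---|---|---|
| 0.5 | 17% | 37% | 65% |
| 0.6 | 43% | 64% | 86% |
| 0.75 | 74% | 88% | 97% |
| 0.8 | 81% | 92% | 99% |
| 1.0 | 96% | 99% | >99% |

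With 23 per arm, the unadjusted figure at 0.5 SD falls to 7%.

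The number per arm for 80% power, unadjusted, by the normal approximation is n = 2 × ((1.645 + 1.282)/margin)². This gives 69 at 0.5 SD, 48 at 0.6 SD, 31 at 0.75 SD and 27 at 0.8 SD.

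**4. What non-significance tells us.** If the true difference were 0.5 SD, a two-sided 5% t-test would be non-significant with probability 62% (23 per arm) or 55% (28 per arm). With 28 per arm, baseline adjustment lowers this to 44% (ρ = 0.5) or 27% (ρ = 0.7). Non-significance is therefore compatible with a moderate difference and cannot stand in for equivalence.

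**The case against.** **The wording sits outside the methods.** The word appears only in the Discussion and its counterpart in the Abstract. Removing it changes no test, outcome or sample size. That is true, and it makes the repair cheap. The sentence is nevertheless a stated inferential step with a stated trigger, and it governs what may be concluded.

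**This is a condensed article, and an analysis plan may exist.** A missing margin or decision rule is not in itself an error here. What remains is that the article promises a conclusion and then states tests and a sample size directed at something else. The 5% level does not exclude equivalence testing, since two one-sided tests are commonly run at 5%. Nor does "No additional analysis will be performed" settle the matter, because its heading gives subgroup analyses as the example.

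Three stronger readings are tempting, and the documents do not support them:

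- *That a null result will be reported as equivalence.* No section says so. A reader may infer it because the article describes no other route, but it remains an inference.
- *That non-significance is the most likely outcome.* This depends on the unknown true effect. The article claims 90% power at its own effect size, hence about 10% non-significance there. With 28 per arm, the unadjusted t-test is non-significant in 55% of trials at 0.5 SD, but in 16% at 0.8 SD and 4% at 1.0 SD. It is also a single-time-point test, not the planned group-by-time ANOVA.
- *That the sample is too small at any useful margin.* The table shows power above 80% at 0.8 SD unadjusted, at 0.75 SD with ρ = 0.5 and at 0.6 SD with ρ = 0.7. Which margin is useful on the pain or function scales needs SDs and clinical thresholds that the article does not give.

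**Conclusion.** The point holds as a mismatch between a promised conclusion and the stated methods. The tests described cannot establish equivalence at any margin, because they do not test for it.

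Whether 56 participants could support a properly specified equivalence test depends on a margin that the article does not state. At 0.5 SD power is low to moderate (17% unadjusted, 37% to 65% adjusted). It becomes adequate only with a wide margin or a strong baseline correlation. For scale, f = 0.25 corresponds to 0.5 SD by the usual two-group conversion (d = 2f), so a margin of 0.75 SD or more would be wider than that difference and would need justification.

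These figures assume truly identical arms, normal outcomes, equal variances, one outcome, one time point and no losses from the 28 per arm. Any true difference or dropout lowers them. The claim should be corrected before results are interpreted. Neither the randomised comparison nor the ANOVA needs to change.

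**What to change.** In the Abstract and in the Discussion, delete the equivalence sentence and put in its place, for example: *If superiority is not shown, the between-group difference will be reported with its 95% confidence interval at 6 weeks (primary) and at 4 and 18 weeks, and no conclusion of equivalence will be drawn from a non-significant test.* This keeps all three time points that the Discussion names.

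If the sponsor wants to keep the claim, it should do the following before data are seen:

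- fix one outcome and one time point, with a margin justified on that outcome's scale;
- state the rule (two one-sided tests, or the matching confidence interval lying inside the margin) and any baseline adjustment;
- state the power at that margin with the planned 56 participants;
- add the step to Statistical methods {20a}.

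The first option costs two sentences and no participants. The trial gives up only a claim that its planned tests cannot support. The second costs a protocol amendment and, at narrow margins, an open statement that power is low.

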### Outcomes {12}

#### Primary outcomes

The primary outcomes will be change in pain scores at the base of the thumb, assessed by VAS (0–100 mm), at rest and during pinch movement from baseline to 6 weeks [30]; change in hand function, evaluated using the Australian/Canadian Hand Osteoarthritis Index (AUSCAN) (0–36) from baseline to 6 weeks [30]; change in values of pinch strength (Lafayette Hydraulic Pinch Gauge (in kg)) from baseline to 6 weeks; and change in magnitude of activation of the abductor pollicis brevis (APB), 1st DI, extensor pollicis brevis (EPB), and abductor pollicis longus (APL) from baseline to 6 weeks.

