#### Secondary outcomes

The secondary outcomes will be change in VAS pain scores (0–100 mm) at the base of the thumb, at rest and during pinch movement from baseline to 4 and 18 weeks; change in hand function, assessed by the AUSCAN function section (0–36) from baseline to 4 and 18 weeks; change in social participation according to the Canadian Occupational Performance Measure (COPM) tool from baseline to 4, 6, and 18 weeks, change in pain based on the AUSCAN pain section (0–20) from baseline to 4, 6, and 18 weeks; change in manual dexterity as per the Nine-Hole Peg Test (NHPT) (expressed in seconds) from baseline to 4, 6, and 18 weeks; change in values of grip strength from baseline to 4, 6, and 18 weeks (Lafayette Professional Hand Dynamometer (in kg)) and pinch strength (Lafayette Hydraulic Pinch Gauge (in kg)) from baseline to 4 and 18 weeks; change in execution time (expressed in seconds) of Bilateral Upper Limb Function Test (BULFT) tasks from baseline to 4, 6, and 18 weeks; and magnitude of activation of the abductor pollicis brevis (APB), 1st DI, extensor pollicis brevis (EPB), and abductor pollicis longus (APL) from baseline to 4 and 18 weeks.

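### The Discussion rests the superiority or equivalence conclusion on secondary visits and a secondary outcome, in conflict with the week-6 primary outcomes

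*Protocol article*

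**What the plan says.** Four places in the protocol article bear on this.

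- **Primary outcomes.** All are changes from baseline to week 6: VAS pain ("at rest and during pinch movement from baseline to 6 weeks"), AUSCAN hand function, pinch strength, and "change in magnitude of activation of the abductor pollicis brevis (APB), 1st DI, extensor pollicis brevis (EPB), and abductor pollicis longus (APL").
- **Secondary outcomes.** The same measures at the other visits are secondary, for example VAS pain "at rest and during pinch movement from baseline to 4 and 18 weeks". Participation is secondary throughout: "change in social participation according to the Canadian Occupational Performance Measure (COPM) tool from baseline to 4, 6, and 18 weeks".
- **Statistical methods for primary and secondary outcomes {20a}.** Groups are compared in every domain, overall and at each assessment stage, by a mixed model ANOVA with post hoc contrasts. "A 5% significance level will be adopted for all analyses". The section does not separate primary from secondary outcomes.
- **Discussion.** The study is to show whether strengthening the first dorsal interosseous "has a superior and positive effect on the clinical picture of patients with CMC OA" or, failing that, whether the two protocols are equivalent. It then gives the basis: "This will be analyzed based on possible changes in some symptoms (i.e., pain, function, activity, and participation"). The time points that it names for these changes are "during the treatment period (4 weeks and 6 weeks), or 3 months after its completion".

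**The concern.** The Outcomes section and the Discussion give different answers to the question of which results decide the trial. The Discussion admits two secondary visits and one secondary outcome, gives week 6 no priority, and omits pinch strength and muscle activation, although Objectives {7} names strength in the main objective. Nothing in the statistical section settles the matter, because it treats all domains and stages alike at 5%.

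At stake is the meaning of the primary/secondary split. All week-6 primaries could be null and the report could still claim superiority from, say, COPM at week 18 without departing from the Discussion. The error rate of such a claim would not be the stated 5%. Reducing the week-6 primaries to one would not remove this problem, because the Discussion wording would still admit the other visits and COPM.

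**Working it through.** **1. The texts side by side**

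| Item | Outcomes section | Discussion basis |
|---|---|---|
| VAS pain, AUSCAN function, week 6 | primary | included |
| Pinch strength, muscle activation, week 6 | primary | not named |
| Pain and function, weeks 4 and 18 | secondary | included |
| Participation (COPM), all visits | secondary | included |

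Table 1 schedules pain, AUSCAN and COPM at session 13, session 18 and follow-up, so each symptom in the Discussion list can be tested at three post-baseline visits.

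**2. The plan's own figure.** The plan states 5% per analysis, taken here as two-sided because the document does not say. For one prespecified comparison, 1 − 0.95¹ = 5%, so the figure is right in that case.

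**3. Several independent tests.** The chance of at least one false positive is 1 − 0.95^k.
- One symptom at three visits, k = 3: 14.3%.
- Three constructs (pain, function, activity/participation) at three visits, k = 9: 37.0%.
- Four measures (VAS at rest, VAS during pinch, AUSCAN function, COPM as one score) at three visits, k = 12: 46.0%.

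**4. Correlated tests.** The document gives no correlations, so these are assumptions. Normal test statistics were simulated with equal correlation between visits and equal correlation between outcomes (product structure), each tested at |z| > 1.96.

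| Family | Correlation 0.3 | 0.5 | 0.7 | 0.8 |
|---|---|---|---|---|
| 1 symptom × 3 visits | 13.5% | 12.5% | 11% | 9.8% |
| 3 × 3 = 9 tests | 34% | 29% | 23% | not run |
| 4 × 3 = 12 tests | 42% | 36% | 26% | not run |

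False results in favour of the intervention, against a nominal 2.5%, are about half of these: 6.3% for one symptom at correlation 0.5, and 11% to 22% across the 9- and 12-test families.

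**5. The case at issue.** In the 12-test family at correlation 0.5, about 23% of null trials have no significant week-6 result for VAS at rest, VAS during pinch or AUSCAN function, yet have at least one significant result elsewhere in the family. The range is 28% to 16% for correlations 0.3 to 0.7. Pinch strength and muscle activation were not modelled; requiring them to fail as well would lower these figures.

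**6. With an omnibus gate.** Suppose contrasts are read only after a significant ANOVA effect (four visits, correlation 0.5, large-sample approximation).
- Gate on the interaction: about 2% for one symptom, 6% for 9 tests, 8% for 12.
- Gate on either group or interaction: about 6%, 16% and 19%.

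**7. Week 6 alone.** As listed there are eight primary measures: two VAS, AUSCAN function, pinch strength counted once, and four muscles. At 5% each, 1 − 0.95⁸ = 33.7% if independent, and about 25% at correlation 0.5. Confining the conclusion to week 6 is therefore not enough on its own.

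**8. Power if eight primaries are adjusted.** The planned 46 participants (f = 0.25, 5%, 90% power) are reproduced by the group-by-time interaction with two measurements and correlation 0.5: λ = N·f²·m/(1 − ρ) = 46 × 0.0625 × 2/0.5 = 11.5, power 0.91. They are also reproduced by the between-group effect with four measurements and correlation 0. At the first Holm step, 0.05/8 = 0.00625, power falls to 0.70 in both. With the stated four measurements and correlation 0.5, the interaction would still have power 0.92.

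**The case against.** The strongest reply is that the Discussion is prose and not a decision rule. It names no test, threshold or success criterion. It says that some symptoms will be considered, not that any one suffices, and the sentence directly follows the equivalence sentence. The Outcomes section sets the hierarchy and nothing revokes it. Strength and activation are arguably not symptoms, so their omission may carry little weight. Multiplicity detail may sit in an analysis plan that is not shown, and the planned ANOVA may act as a gate.

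Much of this stands. A reader might infer a formal rule under which one significant symptom at any visit proves superiority, so that the primary outcomes play no part. The documents do not say that. A reader might also quote an error rate of about 41%. That figure requires AUSCAN pain as a fifth measure (15 tests), assumed correlations of 0.5 and no omnibus gate, and none of these is fixed by the text.

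The conflict itself remains. The Discussion sentence is forward-looking and is the only statement of what the conclusion rests on. Equivalence is posed as the alternative if superiority is not shown, so the sentence most naturally covers both. Read as covering equivalence only, it still departs from the declared primaries. The point does not rest on silence about multiplicity, because the article affirmatively sets 5% for all analyses at each stage and describes a basis that differs from its own primary outcomes. No gate is stated.

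**Conclusion.** The concern holds as a conflict between sections that leaves open a superiority claim from a secondary outcome or visit when the week-6 primaries fail. It does not show that such a claim is planned.

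The size is conditional. With ungated tests at 5%, the chance of at least one false positive is about 12.5% for one symptom at three visits (10% to 14%), and about 23% to 42% for 9 to 12 tests, with about half favouring the intervention. These figures rest on assumed correlations (0.8 to 0.3 for one symptom, 0.7 to 0.3 for the larger families) and on a chosen count of tests. An omnibus gate would lower them, to below 5% for one symptom if the gate is the interaction. The correction should be made before any between-group results are seen.

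**What to change.** Replace the Discussion sentence, and add the same text to the statistical methods section:

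> Superiority will be concluded only from the between-group difference at 6 weeks in one designated primary outcome (or in the listed primary outcomes with Holm adjustment across them). Results at 4 and 18 weeks, and COPM, AUSCAN pain, NHPT, grip and BULFT at all visits, are secondary, will be reported as estimates with 95% confidence intervals, and cannot by themselves support a superiority claim.

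If durability is to be claimed, test week 18 only after week 6 is significant. The choice of a single primary or Holm is a necessary part of the change, because week 6 alone still carries eight measures.

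The cost is wording, with no new data, visits or participants. An isolated week-4, week-18 or COPM result could no longer be called proof of superiority. Under Holm, power per primary falls; at the strictest step it goes from 0.91 to about 0.70 under the assumptions that reproduce 46 participants. Designating one primary avoids that loss.
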